**Fig. 1 Fig1:**
[figure not shown]
Schematic diagram representing overall study design and study visits Legend: IVIg = intravenous immunoglobulin, red triangles represent the treatment visits. The first treatment visit is spread out over 2-4 consecutive days, treatment visit 2-4 will consist of 1-2 consecutive days

In brief, after a screening period of ≤ 10 days, eligible subjects are randomized to receive either IVIg at an uploading dose of 2 g/kg body weight (bw), ideally over 2–4 (consecutive) days, or a matching placebo. Thereafter, a study drug infusion is administered every 3 weeks at a dose of 1 g/kg bw, given over 1–2 (consecutive) days for a total of three additional infusions following baseline. The subjects’ pain is measured using Pain Intensity Numerical Rating Scale (PI-NRS) at baseline and at each study visit scheduled every 3 weeks for 12 weeks. Pain is also assessed twice a day (daytime and nocturnal pain, through PI-NRS) on 2 days each week (Monday and Friday). A responder is defined as a ≥ 1-point improvement on the mean weakly peak pain using the PI-NRS relative to baseline. Patients who show an improvement and complete the 12 weeks of study treatment will be followed during a 3-month-extension phase to determine the long-term effect of the received therapy on pain alleviation.

The study is placebo-controlled because in previous analgesic trials a placebo effect of 7-37 % has been shown [32]. To make sure IVIg has a factual effect on pain reduction, a placebo-controlled design is necessary to exclude the placebo effect of this treatment on the patients. In addition, patients are allowed to use pain medication that not has been changed in the 30 days prior to randomization. As a result, in case the patient receives a placebo, the treatment does not differ from the situation before participating in the study.

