#### Secondary outcomes

Secondary outcome measures include changes in the daily pain intensity, nocturnal pain intensity, and the average of these two obtained from the PI-NRS, change in patients’ global impression of change (PGIC) [38, 39], the Rash-transformed 13-item SFN Symptoms Inventory Questionnaire (RT-SFN-SIQ) [40], the amount of pain medication, the use of nonmedical rescue activities, the amount of pain relief (using a 5-point Likert-scale), the NPS [34], the Daily Sleep Interference Scale (DSIS), the Short Form 36 Health Survey (SF-36) [41, 42], and the Rasch-built Overall Disability Outcome Scale (SFN-RODS) [40].

Safety evaluation features will include the following additional tests: adverse events, laboratory test (e.g., hematology and clinical chemistry, as shown in Table 2), and vital signs.

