#### Type of analysis

The primary efficacy comparison is the comparison of the proportion of responders in the per-protocol population, where a responder is defined as ≥ 1-point improvement in the mean weekly peak pain measured with the PI-NRS (maximum pain) during the 12-week treatment period after first study drug infusion compared to baseline, using Kaplan-Meier curves (log rank test). The following sensitivity analyses will be performed. The primary efficacy analysis will be repeated in the per-protocol population using a more strict definition of a responder: a “responder of ≥ 2 points” is defined as ≥ 2 points improvement in the PI-NRS at the last evaluation after the first study drug infusion during the blinded 12-week treatment period compared to baseline.

In the intention-to-treat (ITT) population, the following additional sensitivity analyses will be performed: any subject who drops out with at least the week 6 PI-NRS assessment with their last mean weakly peak pain on the PI-NRS will be carried forward. A subject dropping out before the week 6 PI-NRS assessment or any subject with no baseline PI-NRS will be counted as a nonresponder independent of the last PI-NRS. Furthermore, in the ITT population, the following sensitivity analyses will be performed. The analysis will be repeated using a more strict definition of a responder: a “responder of ≥ 2 points” is defined as ≥ 2 points improvement in the PI-NRS at the last evaluation following the first study drug infusion during the blinded 12-week-treatment period compared to baseline. Subjects with no baseline or no postbaseline PI-NRS assessment will be counted as a nonresponder in this analysis.

When values are missing, we will use multiple imputation based on a regression method, using SPSS (IBM Corp. Released 2015. IBM SPSS Statistics for Macintosh, Version 22.0. Armonk, NY: IBM Corp) or Stata (StataCorp. 2013. Stata Statistical Software: Release 13. College Station, TX: StataCorp LP).

The differences between the per-protocol analyses and the ITT analyses will give a good impression of the bias that might occur in the study. Comparing these two methods, we can make a clear picture of the two populations and can investigate the true effect of IVIg in the most reliable way.

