The secondary efficacy variables will be tested for treatment group differences by analyses of covariance (ANCOVAs) with the baseline measurement as the covariate and the difference of the last post-baseline measurement in the treatment period relative to baseline as an independent variable (treatment group as fixed factor). If no postbaseline measurement is documented, the baseline measurement will be used as the last postbaseline measurement. This analysis is an endpoint analysis using the “last observation carried forward” (LOCF) approach.

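### For the three diary pain outcomes the secondary analysis uses only the last measurement, so most of the late-treatment ratings already collected are unused and precision is lost

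*Protocol article*

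**What the plan says.** All references are to the protocol article.

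- **Collection.** Study design (text below Fig. 1) schedules the PI-NRS "at baseline and at each study visit scheduled every 3 weeks for 12 weeks" and adds a diary: "Pain is also assessed twice a day (daytime and nocturnal pain, through PI-NRS) on 2 days each week (Monday and Friday".
- **Outcomes.** Secondary outcomes lists "changes in the daily pain intensity, nocturnal pain intensity, and the average of these two obtained from the PI-NRS".
- **Analysis.** Type of analysis gives one rule for all secondary efficacy variables: "analyses of covariance (ANCOVAs) with the baseline measurement as the covariate", applied to "the difference of the last post-baseline measurement in the treatment period relative to baseline". It calls this an endpoint analysis with last observation carried forward. It names no weekly mean and no end-of-treatment window.
- **Contrast.** For the primary outcome the same section does specify an averaged unit: "improvement in the mean weekly peak pain measured with the PI-NRS (maximum pain) during the 12-week treatment period".

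**The concern.** One generic rule covers two very different kinds of data. Questionnaires such as the SF-36 and SFN-RODS are completed at three-weekly visits, so taking the last value leaves little aside. The diary has two rating days in every week. For a diary outcome, the last value is one day out of about 24, or two days out of about 24 if a weekly mean was intended.

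This applies even to a patient with a complete diary. It is therefore separate from the question of how missing values are filled in. A single day carries that day's random fluctuation in full, which widens the confidence interval for the treatment difference. Pain intensity comes first in the article's list of secondary objectives, and the trial has only 60 patients. The averaging used for the primary outcome shows that an averaged unit was available.

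**Working it through.** **The plan's own figure.** The article states no power or precision for any secondary outcome. Its only such figure is the primary sample size, from response rates of 25 % and 60 %, one-sided 5 % and 80 % power:

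n = [1.645·√(2 × 0.425 × 0.575) + 0.842·√(0.25 × 0.75 + 0.60 × 0.40)]² / 0.35² = (1.150 + 0.550)² / 0.1225 ≈ 23.6, so 24 per group, and 24 / 0.80 = 30 after dropout.

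This agrees with the article, and the present point does not affect it.

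**Inputs**

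- Diary days: 2 per week × 12 weeks = 24 (Study design).
- Days used by the rule: 1 of 24 (about 4 %) on the last-day reading; 2 of 24 (about 8 %) on the last-weekly-mean reading.
- Days in weeks 10 to 12: 3 × 2 = 6. These follow the week-9 infusion visit.
- Day-to-day share of the variance, w: not given in the documents. Assumed 0.2 to 0.5.

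**Formula.** With independent day-to-day noise, the variance of a mean of k diary days relative to one day is

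R(k) = (1 − w) + w/k.

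The ratio of standard errors for six days against k days is √[R(6)/R(k)].

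| w | R(1) | R(2) | R(6) | SE cut, 6 days against 1 | SE cut, 6 days against 2 |
|---|---|---|---|---|---|
| 0.2 | 1 | 0.900 | 0.833 | 1 − √0.833 = 8.7 % | 1 − √0.926 = 3.8 % |
| 0.3 | 1 | 0.850 | 0.750 | 1 − √0.750 = 13.4 % | 1 − √0.882 = 6.1 % |
| 0.5 | 1 | 0.750 | 0.583 | 1 − √0.583 = 23.6 % | 1 − √0.778 = 11.8 % |

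**Sensitivity to the baseline covariate.** The table gives no credit for baseline adjustment. Take equal correlation ρ = 1 − w between all diary days and a one-day baseline. The ANCOVA residual variance is then R(k) − ρ².

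- w = 0.2: 1 − 0.64 = 0.360 for one day, 0.833 − 0.64 = 0.193 for six days. SE cut 1 − √(0.193/0.360) ≈ 27 %.
- w = 0.5: 1 − 0.25 = 0.750 for one day, 0.583 − 0.25 = 0.333 for six days. SE cut 1 − √(0.333/0.750) ≈ 33 %.

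Adjustment removes stable differences between patients, so noise is a larger share of what remains and the relative gain rises. Equal correlation is favourable to averaging, because slow drift within a patient averages out less well. With a slowly varying component added (20 to 30 % of the variance, weekly autocorrelation 0.8) and a two-day baseline, a four-day mean cuts the SE by 15 to 24 % and an eight-day mean by 21 to 31 %. The 9 to 24 % range is therefore a cautious one.

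**The case against.** **The article does not define a measurement for a diary outcome.** It could mean the last diary day, the last weekly mean or the week-12 visit PI-NRS in Table 1. Elsewhere the PI-NRS unit is a weekly mean, and for the primary outcome it is a weekly mean that is carried forward. This stands in part. A reader might infer that a single rating is certainly what will be analysed, and the text does not go that far. The weekly-mean reading reduces the gain to about 4 to 12 % but does not remove it. The visit reading would not rescue the plan, since it too is one occasion and daytime and nocturnal pain are described as diary ratings.

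**Such detail belongs in the full protocol or SAP.** That would answer a complaint that something is missing. Here the article states the analysed value and calls it an endpoint analysis; the point is about that stated choice.

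**Stakes are limited.** The article calls the trial a pilot, and no secondary outcome is powered. It might be inferred that these are the only continuous pain-intensity comparisons among the secondary outcomes. They are not: the NPS is also listed, and the inclusion criteria use its first question to rate pain intensity. For the average outcome, one day's value already combines two ratings, so its gain may be smaller. All of this stands.

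**A window creates its own problems.** A mean over weeks 10 to 12 is undefined for patients who leave earlier, and about 20 % dropout is planned. The article does not say that the diary starts before treatment. Both are fair, and the fix must deal with them.

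**Conclusion.** The point holds as a matter of efficiency. On either natural reading, at most two of about 24 diary days enter the analysis of daytime, nocturnal and average pain. Averaging the six days of weeks 10 to 12 would cut the standard error by about 9 to 24 % against a single day and about 4 to 12 % against a last weekly mean. This rests on an assumed day-to-day share of 20 to 50 % and on independent day-to-day noise.

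Two stronger conclusions are not supported. First, a reader might infer that the treatment comparison is biased or invalid. Day-to-day noise affects both arms alike and only widens the interval; any bias from carrying values forward is a different matter. Second, a reader might want a power figure. The half-SD rule under Sample size implies an SD of about 2. Treating that as the residual SD gives 48 % power for a 1-point difference with one rating, 30 per arm and two-sided 5 %. Crediting a one-day baseline correlated at 0.5 to 0.8 gives 61 to 90 %. That spread shows that absolute power should not be quoted. Only the relative gain is usable.

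**What to change.** For daytime, nocturnal and average PI-NRS only, replace the last-measurement rule with:

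- **Endpoint:** the mean of all diary ratings available in weeks 10 to 12.
- **Patients with no rating in that window:** handled by a named method that the plan already states, for example the regression-based multiple imputation under Type of analysis. The same section prescribes last observation carried forward for secondary variables, so the text should say which one applies here.
- **Covariate:** the baseline PI-NRS, or the mean of the pre-treatment diary ratings if these are collected.
- **Model:** ANCOVA otherwise unchanged. The visit-based questionnaires can keep their present rule.

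The cost is two or three sentences and no new data. The article says recruitment had yet to start, so the change could be prespecified. The small downside is that the estimate describes the last three weeks of treatment and not the final day, which should be stated as the intended target.

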## Discussion

In this study, the efficacy and safety of IVIg is evaluated in patients with skin-biopsy-proven idiopathic SFN. This will be the first randomized, placebo-controlled, double-blind, clinical trial with IVIg versus placebo in patients with SFN.

In previous case studies with patients diagnosed with SFN and an underlying autoimmune disease (such as sarcoidosis, Sjögren’s syndrome, and celiac disease), IVIg has shown to be effective on chronic pain [20, 21, 24]. In addition, in chronic refractory pain in general, pain reduction after IVIg treatment has been described [23], suggesting that immunological mechanisms may play a role in the development or maintenance of pain, even if no clear immunological disorders are present.

One of the limitations of the study is that the specific mechanism of action of IVIg is not known, making it hard to predict which patients will benefit from the treatment. A second limitation might be that the treatment period of 3 months is too short to obtain effect. Third, patients will be kept stable on their current pain treatment, which could influence the results. However, stopping current pain medication would be ethically difficult.

In SFN, a better treatment is warranted because currently available (neuropathic) pain medication does not relieve pain substantially and often has side effects [44]. For IVIg, both a complementary and diminishing action on the immune system has been described [45]. In SFN, an activated immune system probably causes inflammatory responses to the small nerve fibers, which can be diminished by IVIg.

Positive findings of IVIg treatment in SFN will result in a new treatment option and may support an immunological role in this condition.

### Trial status

Participant recruitment will start at the half of 2016.

## Abbreviations

Bw, body weight; DSIS, Daily Sleep Interference Scale; eCRF, electronic case report file; GCP, good clinical practice; ICH, International Council for Harmonisation; IENFD intraepidermal nerve fiber density; IMMPACT, Initiative on Methods, Measurements and Pain Assessment in Clinical Trials; I-SFN, idiopathic small fiber neuropathy; ITT, intention-to-treat; IVIg, intravenous immunoglobulin; LOCF, last observation carried forward; MCID, minimum clinically important difference; NPS, Neuropathic Pain Scale; PGIC, Patients’ Global Impression of Change; PI-NRS, Pain Intensity Numerical Rating Scale; RT-SFN-SIQ, Rasch-Transformed Small Fiber Neuropathy Symptoms Inventory Questionnaire; SAE, serious adverse event; SF, 36 Short Form 36 Health Survey; SFN, small fiber neuropathy; SFN-RODS, small fiber neuropathy Rasch-built Overall Disability Outcome Scale; WBP, Wet Bescherming Persoonsgegevens
